**Figure 1 F1:**
[figure not shown]
Study flowchart. On referral for vascular access creation, patients are screened for eligibility. Patients who meet the inclusion and exclusion criteria and provide informed consent will be randomised and allocated to one of the treatment strategies. Follow-up for the primary and secondary outcomes starts at the moment of treatment allocation. PROM, patient-reported outcome measure.

### External validation of a mortality prediction model

Elderly haemodialysis patients form a heterogeneous population in terms of comorbidities and life expectancy. The majority of elderly haemodialysis patients have multiple comorbidities and a relatively short life expectancy, making the long-term performance of the vascular access less relevant. However, for the small group of elderly patients with an unusually long life expectancy, autologous arteriovenous fistulas are considered to be the best vascular access, given their low complication rates after maturation. To identify this subset of elderly patients that should be excluded from randomisation, we performed an external validation of the mortality prediction score developed by Dusseux *et al*.^17^ This prediction score contains items readily identified from the medical history and can be completed before initiation of haemodialysis treatment.

The mortality prediction score was validated in the Netherlands Cooperative Study on the Adequacy of Dialysis (NECOSAD).^18 19^ In this multicentre observational cohort study, adult patients starting dialysis treatment between 1997 and 2007 in the Netherlands were prospectively followed up until 1 February 2015. For the current validation, we restricted the sample to haemodialysis patients aged 70 years and older. This resulted in 494 patients, 411 of whom died during follow-up with a median survival of 2.3 years (IQR 1.1–4.4 years). Overall, baseline characteristics in the validation cohort were comparable to those in the Dusseux cohort (table 1).^17^ Missing data were assumed to be largely missing at random. Therefore, 10-fold multiple imputation with fully conditional specification was performed using the R package ‘mice’. All variables of the mortality prediction score and the outcome were included in the imputation model.^20 21^

**Table 1 T1:** Baseline characteristics of the NECOSAD validation cohort compared with the Dusseux derivation cohort^17^

	NECOSAD cohort n=494	Dusseux cohort n=8955
Gender (male) (%)	61	60
Age (years)	76 (73–79)	78 (74–82)
Diabetes (%)	25	38
Ischaemic heart disease (%)*	31	14
Peripheral vascular disease (%)	24	27
Cerebrovascular disease (%)	14	12
Congestive heart failure (%)	19	34
Dysrhythmia (%)†	22	25
Respiratory disease (%)‡	12	13
Active malignancy (%)	4	11
Psychiatric disorder (%)§	3	4
Mobility (%)¶**		
Walks without help	64	69
Needs assistance for transfers	32	22
Totally dependent for transfers	4	9
BMI (kg/m^2^) (median, %)††		
<21	13	18
22–25	43	35
25–30	33	33
>30	10	14
Central Venous Catheter at dialysis initiation (%)	23	42

*Ischaemic heart disease was defined as a history of angina pectoris or myocardial infarction.

†Vitamin K antagonist use was used as a proxy for cardiac dysrhythmia.

‡Respiratory disease was defined as the need to take pulmonary medication on a daily basis.

§Psychiatric disorder was defined as dementia, depression or other psychiatric disease.

¶The Karnofsky score was used as a proxy for mobility, where a score of >60 was considered as ‘walks without help’, a score of 50–60 as ‘needs assistance for transfers’ and a score of <50 as ‘totally dependent for transfers’.

**32% of the data concerning mobility was missing in the Dusseux cohort.

††29% of the data concerning BMI was missing in the Dusseux cohort.

BMI, body mass index; NECOSAD, Netherlands Cooperative Study on the Adequacy of Dialysis.

Each individual’s risk score was calculated with the original point system as presented by Dusseux (online supplemental data 1). Risk scores ranged from 0 to 28, with a higher score corresponding to a higher risk of mortality. From the individual risk scores, the discrimination for mortality within 2 years was assessed by c-statistics that were pooled over the 10 imputation datasets according to Rubin’s rules.^22^ The Dusseux mortality risk score had a c-statistic of 0.68 (95% CI 0.63 to 0.73) in the NECOSAD validation cohort. Furthermore, the cohort was divided into five groups with increasing mortality risk. A calibration plot of predicted versus observed mortality risk was computed. Calibration was moderate as the model tended to overpredict the mortality risk (53% average predicted risk and 38% average observed risk, figure 2). Finally, we determined a sensible cut-off point for identifying a subset of patients with an unusually long life expectancy. A cut-off between a score of ≤4 and ≥5 was chosen to separate patients with unusually good outcomes (consisting of 22% of patients in the validation cohort with a median survival of 5.0 years, 95% CI 4.3 to 5.4) from elderly haemodialysis patients with a poor life expectancy (consisting of the remaining 78% of patients in the validation cohort with a median survival of 2.2 years, 95% CI 1.9 to 2.5; figure 3).

10.1136/bmjopen-2021-053108.supp1Supplementary data

**Figure 2 F2:**
[figure not shown]
Calibration plot presenting the mortality risk as predicted by the Dusseux risk score and the observed risk in the Netherlands Cooperative Study on the Adequacy of Dialysis cohort, such that the 45° line indicates perfect agreement between predicted and observed risks.

**Figure 3 F3:**
[figure not shown]
Kaplan-Meier curve comparing the survival probability for the high risk and the low risk groupS in the Netherlands Cooperative Study on the Adequacy of Dialysis cohort.

### Interventions

The surgical strategies in the usual care and intervention groups are part of standard clinical care. Because we aim to compare the different surgical strategies for vascular access creation in everyday practice, we will not interfere with surgical protocols at the study sites. However, we expect the study sites to follow current best practice and guideline recommendations.^5^

#### Autologous arteriovenous fistulas

Fistulas are preferably created at the most distal site with adequate blood vessels, in the non-dominant arm. It is recommended to create the fistula 3–6 months before the expected start of haemodialysis treatment. In case of fistula failure, a new arteriovenous fistula may be created at the next available site.

#### Prosthetic arteriovenous grafts

Patients who are allocated to the graft strategy will have a commercially available prosthetic vascular graft implanted for haemodialysis access. It is recommended to place the arteriovenous graft 2 weeks before the expected start of haemodialysis treatment with antibiotic prophylaxis. Placement of an early-cannulation graft is recommended for patients who require a more urgent start of haemodialysis to avoid the use of a temporary central venous catheter. In case of graft failure despite thrombectomy, a new graft may be placed.

#### Central venous catheters

Patients who are allocated to the catheter strategy will have a dialysis catheter inserted, unless they have already started haemodialysis with a tunnelled catheter. We recommend placing a tunnelled catheter just before the start of haemodialysis treatment. We advise following published guidelines for the prevention and treatment of catheter infections.^23^ In case of catheter dysfunction despite local thrombolytic agents, the catheter can be exchanged.^24^

For the arteriovenous fistula and graft group, surveillance and pre-emptive intervention for stenosis will take place according to usual practice at the study sites. In case of failure, both endovascular and surgical interventions can be undertaken to restore patency. If the assigned vascular access strategy proves not to be feasible, patients will cross over to one of the other treatment groups after discussion of the case with the principal investigator. Use of a temporary central venous catheter is not considered as a treatment group crossover.

### Primary study outcome

The primary study outcome is the number of access-related interventions required for each person-year of haemodialysis treatment. To analyse this, we will divide the total number of interventions during follow-up by the total number of haemodialysis years. The primary outcome corresponds to the proposed core outcome measure for haemodialysis vascular access.^25^ This outcome measure includes all percutaneous access interventions, surgical access procedures and catheter interventions from randomisation until the end of the study period or death. The outcome measure specifically includes interventions before dialysis initiation and after dialysis cessation in the occasional patient who stops haemodialysis treatment after kidney transplantation, peritoneal dialysis, recovery of renal function or refusal of further haemodialysis. These vascular access interventions before dialysis initiation and after dialysis cessation are included as they are part of the standard care that this trial evaluates. Patients who discontinue haemodialysis treatment will therefore remain in the trial. Access-related complications that are resolved using conservative or pharmacological treatment are not counted as interventions.

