Clinical practice guidelines on vascular access have long recommended the creation of autologous arteriovenous fistulas regardless of patient characteristics.^5^ However, this recommendation is based solely on observational studies that are at high risk of bias. Patients who have a fistula created prior to starting dialysis generally have more favourable baseline characteristics and a lower mortality risk than other patients.^6^ These favourable patient characteristics may account for two-thirds of the survival benefit seen in patients using arteriovenous fistulas for haemodialysis treatment instead of central venous catheters.^7^ Further selection bias will occur as patients are analysed according to vascular access use. This tends to favour autologous fistulas since the poor subset of patients with fistulas that have failed to mature will go on to use a different type of vascular access. When primary fistula failures are taken into account, the cumulative patency of fistulas and grafts become comparable.^8^ Finally, observational studies based on dialysis registries do not include patients with arteriovenous fistulas created before dialysis initiation that were never used because of patient death or stable renal function.

Uncertainty regarding the best type of vascular access is particularly important for elderly patients starting haemodialysis treatment. In these patients, autologous arteriovenous fistulas have a 40% increased risk of non-maturation and early failure.^2^ Moreover, 30% of fistulas created before initiation of dialysis treatment in elderly patients will never be used because of patient death, stabilisation of renal function or choice for conservative treatment as the patient’s condition worsens over time.^9^ Furthermore, the increase in long-term complications associated with arteriovenous grafts may be less relevant for elderly patients with a limited life expectancy. Finally, elderly patients have a 30% lower risk of complications of central venous catheters, including bloodstream infections.^4 10^ Considering this clinical equipoise, the need for better evidence on vascular access strategies in elderly haemodialysis patients is broadly recognised. Indeed, international experts on vascular access surgery as well as patient representatives have called for a randomised trial comparing vascular access strategies in elderly haemodialysis patients.^5 11^

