#### Exclusion criteria

Patent arteriovenous fistula or graft already in place.Prior unsuccessful arteriovenous fistula or graft vascular access surgery.Kidney transplantation scheduled within 6 months.Metastatic malignancies or other condition associated with a life expectancy of <6 months, in the opinion of the attending nephrologist.Unable to provide informed consent.Dusseux risk score of ≤4, indicating an unusually long life expectancy.^17^

Patients will be enrolled by local investigators if they meet the eligibility criteria and provide informed consent. Local investigators will be informed of treatment assignment through a web-based service, after which vascular access creation is planned according to usual clinical care for the allocated vascular access type at the study site (figure 1). The treatment allocation sequence is generated by an independent data management centre using a computer-based random number-producing algorithm. Block randomisation is implemented with randomly varying block sizes of 3 and 6, and randomisation will be stratified by treatment centre. Follow-up starts immediately after treatment allocation.

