### Data analysis plan

The access-related intervention rates will be analysed using a general linear model with Poisson distribution and identity link, and with time as off-set variable. Both intervention (ie, the prosthetic arteriovenous graft and central venous catheter) groups will be compared with the usual care (autologous arteriovenous fistula) group. Non-adherence to the allocated treatment group is expected as patients cross over to another surgical strategy for vascular access when the randomised strategy is no longer feasible. The primary analysis will be on the intention-to-treat population. Exploratory on-treatment analyses will be performed as well. A subgroup analysis will be performed for patients who had already started haemodialysis using a catheter before inclusion.

Formal statistical comparisons will be made for the following secondary study outcomes:

SF-12/DSI and SF-VAQ summary scores using generalised estimating equations.The number of access-related serious adverse events per person-year using general linear models with Poisson distribution and mortality using Cox regression.The number of days admitted to the hospital or visiting outpatient clinics for any reason per person-year using Student’s t-tests.

Primary outcome data are not expected to be missing, as interventions on vascular access will be reported in the patients’ medical files. We expect little to no loss to follow-up since study participants will be observed three times per week in the dialysis unit and the trial requires no additional study visits. PROMs will be analysed using generalised estimating equations that allow for missing data. Other missing data will be handled by using 10 imputation cycles with regression methods, performing standard analyses for each imputation cycle and considering the variability across the imputation cycles in the final analysis.

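### The primary outcome (interventions per haemodialysis-year, counted from randomisation) and the primary model (Poisson, identity link, undefined time offset) do not fit together for patients who never start dialysis

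*Protocol article*

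**What the plan says.** Under Primary study outcome the protocol article states: "The primary study outcome is the number of access-related interventions required for each person-year of haemodialysis treatment". The calculation given is "we will divide the total number of interventions during follow-up by the total number of haemodialysis years". The numerator covers percutaneous, surgical and "catheter interventions from randomisation until the end of the study period or death". It goes on: "The outcome measure specifically includes interventions before dialysis initiation and after dialysis cessation". The reason given is that these procedures belong to the care under evaluation. Under Exclusion criteria, "Follow-up starts immediately after treatment allocation".

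Under Data analysis plan, intervention rates are analysed with a Poisson model and identity link, "with time as off-set variable". The primary analysis is by intention to treat. The text does not say whether time is haemodialysis time or time since randomisation, or how a patient with interventions but no haemodialysis time is handled.

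Patients may be randomised up to 6 months before dialysis is expected (Inclusion criteria). The Introduction says that "30% of fistulas created before initiation of dialysis treatment in elderly patients will never be used because of patient death", stable renal function or a choice for conservative care. Recommended timing of access creation differs by arm: 3-6 months ahead of dialysis for a fistula, 2 weeks for a graft, and for the catheter arm "We recommend placing a tunnelled catheter just before the start of haemodialysis treatment".

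**The concern.** Three stated rules have to hold together: a numerator from randomisation over haemodialysis-years, a Poisson rate model with a time term, and inclusion of every randomised patient. A patient who never starts dialysis tests all three, because that patient can have a count of one or more and no haemodialysis time.

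Such patients are foreseeable from the eligibility criteria and from the protocol's own 30% figure. They are also unlikely to carry equal numbers of procedures in each arm, since fistulas are made earliest and catheters last. How they are handled can therefore change the primary contrast, not just its precision. The Introduction faults registry studies for leaving out fistulas that were created but never used. An analysis that dropped never-starters would repeat that omission inside the trial.

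**Working it through.** **1. The plan's own figure.** Inputs from Sample size calculation: 2.48 interventions per year with a fistula, a reduction of 0.80 (so 1.68), two-sided alpha 0.025, 80% power, 1 year each.

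n per arm = (2.241 + 0.842)² × (2.48 + 1.68) / 0.80² = 9.505 × 6.5 = 61.8, so 62. Power at 65 per arm is 0.82. The stated 65 is reproduced, slightly on the safe side, and is not the source of the problem. It does treat a year of follow-up as a year of haemodialysis.

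**2. What each reading of time does.** Let y be a patient's count and t the time.

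- *Haemodialysis time as multiplier, mean = t × rate.* With t = 0 the mean is 0, and y ≥ 1 has log-likelihood y·log(0), which is minus infinity. Test fits with such rows failed, both with the identity link and with a log link using a log(t) offset.
- *Time since randomisation as multiplier.* The fit runs and keeps everyone, but estimates interventions per year of follow-up. That is not the stated outcome.
- *Literal additive offset under the identity link, mean = a + b × arm + t.* The fit runs, but each extra year is forced to add exactly one intervention. Neither a nor b is a rate per year.

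**3. How far the handling moves the contrast.** Assumptions not in the documents: 1 year per patient, 70% enrolled before dialysis, one procedure per fistula never-starter and none per comparator never-starter. The 30% never starting is the protocol's figure for unused fistulas. Never-starters are 0.70 × 0.30 = 0.21 of each arm, or 65 × 0.21 = 13.7 patients.

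| Handling | Fistula | Comparator | Difference |
|---|---|---|---|
| Ratio of totals | 2.48 + 0.21/0.79 = 2.75 | 1.68 | 1.07 |
| Never-starters dropped | 2.48 | 1.68 | 0.80 |
| Time since randomisation | 2.48 × 0.79 + 0.21 = 2.17 | 1.68 × 0.79 = 1.33 | 0.84 |

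Dropping also lowers power in this scenario to 0.715. With 30-90% pre-dialysis, 10-30% never starting, and 1 to 1.5 procedures per fistula never-starter, the ratio-of-totals difference runs from 0.83 to 1.35, and that on time since randomisation from 0.81 to 0.99. If comparator never-starters also have one procedure each, the ratio of totals gives 2.75 − 1.95 = 0.80, the same as dropping; time since randomisation gives 0.63.

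**4. Size with the planned variable follow-up.** Median survival of 2.2 years (protocol) gives a hazard of ln 2 / 2.2 = 0.315 per year. Two years' recruitment with close-out 1 year after the last patient gives potential follow-up of 1 to 3 years, taken as uniform. Mean follow-up is then 1.46 years. Assume dialysis starts 0.25 to 0.5 years after randomisation in pre-dialysis patients and 30% never start, deaths while waiting included. Mean haemodialysis time per pre-dialysis patient is 0.7 × 1.315 = 0.92 years (0.25 delay) or 0.7 × 1.162 = 0.81 years (0.5 delay).

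Rate removed by dropping = (65 × p × 0.30 × 1) / arm haemodialysis-years, where p is the pre-dialysis share:

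- p = 0.5: 9.75 / 77.2 = 0.13 (0.25 delay); 9.75 / 73.8 = 0.13 (0.5 delay).
- p = 1: 19.5 / 59.8 = 0.33 (0.25 delay); 19.5 / 52.9 = 0.37 (0.5 delay).

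That is 16% to 46% of 0.80. Removing waiting-time deaths first and then a further 30% would give 0.43, but the protocol's 30% already includes death, so that counts death twice.

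**5. Does a workable fit exist?** Yes. In an arm-only model with mean = t × rate, the estimate is total count over total time. Fitting arm totals, or giving zero-time patients a negligible positive exposure, returns the ratio of totals under the planned identity link.

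**The case against.** The best defence is that the outcome section already answers the question. It states that off-dialysis procedures count, gives the ratio of totals, and keeps patients who discontinue dialysis in the trial. The analysis section does not give the unit of data, and a Poisson model on arm totals returns exactly that ratio. On this reading the two sections agree, and naming the offset is detail for an analysis plan that is not shown. Counting off-dialysis procedures per haemodialysis-year is also a deliberate choice with a stated reason, and is not at fault.

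Much of this stands. A reader might infer that the plan drops never-starters and is therefore biased towards fistula. The documents do not support that: no passage says anyone is dropped, intention to treat is stated, and the plan's own ratio keeps these procedures and so raises the fistula rate. A reader might also infer that patients with only days of dialysis would dominate an identity-link fit. They would not, because an arm's estimate is total events over total time and such a patient adds little beyond the count.

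Two limits on the size also stand. The 100% pre-dialysis bound is extreme, because the trial also enrols urgent catheter starters. The 30% is a literature figure, and the eligibility criteria may make it lower here.

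The defence does not remove the mismatch. The ratio of totals is recovered only if the reader supplies haemodialysis time, a multiplicative role for it, and arm-level data or a special rule for zero exposure. The article states none of these, and an offset taken at its word with an identity link does something else.

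**Conclusion.** The point holds as an inconsistency between the stated primary outcome and the stated primary model. As written, the model does not deliver the outcome for all randomised patients, and the sensible ways of completing it give different answers.

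The direction is not fixed by the documents. Dropping never-starters would favour fistula in the comparison with catheter by roughly 0.13 to 0.37 interventions per haemodialysis-year, under the assumptions in step 4 of the working. The ratio of totals avoids this. If comparator never-starters have one procedure each, dropping and pooling agree. The graft comparison is not sized separately; the effect there depends on how many procedures graft never-starters have.

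This concerns the primary analysis, so it should be settled before the data are analysed.

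**What to change.** In the Data analysis plan, and in the analysis plan if one exists, state that:

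- exposure is haemodialysis-years and enters as a multiplier, mean = time × rate;
- every randomised patient's interventions stay in, including those of patients with no haemodialysis time;
- each arm's rate is total interventions over total haemodialysis-years, as the outcome section already says;
- the two rate differences from the fistula arm are tested with a patient-level bootstrap or a sandwich (ratio-estimator) variance.

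Add one supportive analysis with time since randomisation as exposure, labelled as a different quantity. No change of link is needed for the estimate.

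The cost is revised wording and one extra analysis. No new data are needed.
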